# Protocol of the TREASURE study: Thoracic RadiothErapy with Atezolizumab in Small cell lUng canceR Extensive disease – a randomized, open-label, multicenter phase II trial

**DOI:** 10.1186/s12885-022-10074-9

**Published:** 2022-09-24

**Keywords:** Extensive disease small cell lung cancer, SCLC, Radioimmuntherapy, Thoracic radiotherapy, Atezolizumab, Anti-PD-L1 monoclonal antibody, First-line therapy

## Abstract

**Background:**

Recently, the combination of the programmed death-ligand 1 (PD-L1) inhibitor atezolizumab with first-line chemotherapy has demonstrated to improve outcome for patients with advanced small cell lung cancer (SCLC), leading to approval of this regimen. At the same time, accumulating (pre-)clinical data suggest synergisms of radiotherapy and immunotherapy via the radiation-mediated induction of anti-tumor immunogenicity. Combining the recent findings, the TREASURE trial aims at further enhancing response to upfront chemo-immunotherapy by the addition of thoracic radiotherapy (TRT).

**Methods/design:**

The TREASURE trial is a randomized, multicenter, phase II clinical trial (ClinicalTrials.gov identifier, NCT04462276). One hundred four patients suffering from extensive disease (ED) SCLC, with any response to the standard of care induction chemo-immunotherapy will be randomized to receive atezolizumab maintenance therapy with or without TRT. The primary endpoint of this study is overall survival (OS). Secondary endpoints include further measures of efficacy, safety, and the collection of biomarker samples. A safety interim analysis will take place after *n* = 23 patients receiving TRT have been observed for three months after the end of TRT.

**Discussion:**

This trial will investigate whether treatment efficacy can be improved by adding TRT to atezolizumab maintenance therapy in ED SCLC patients with any response after chemo-immunotherapy. Safety and feasibility of such a regimen will be evaluated, and biomaterials for a translational research project will be collected. Together, the results of this trial will deepen our comprehension of how checkpoint inhibition and radiotherapy interact and contribute to the evolving landscape of SCLC therapy.

**Trial registration:**

Clinicaltrials.gov identifier: NCT04462276 (Date of initial registration: 8th July 2020), https://clinicaltrials.gov/ct2/show/NCT04462276

Eudra-CT Number: 2019-003916-29 (Date of initial registration: 30th March 2020), https://www.clinicaltrialsregister.eu/ctr-search/trial/2019-003916-29/DE

## Background

With around 12 -15% of lung cancer cases worldwide, small cell lung cancer (SCLC) is one of the main causes of cancer-related mortality [1]. This aggressive tumor entity frequently shows early development of widespread metastases. Thus, the majority of patients present at a stage of extensive disease (ED), and it is of major importance to develop strategies to improve the outcome of these patients.

One approach that has been explored in the past is the addition of thoracic radiotherapy (TRT) to chemotherapy. In a phase III randomized trial, Slotman et al demonstrated an increased 2-year survival rate with low toxicity rates for patients who received TRT (30 Gray [Gy] in 10 fractions) in addition to prophylactic cranial irradiation (PCI) after any response towards standard chemotherapy, compared to patients who did not receive TRT [2]. Progression was less likely in the TRT group (hazard ratio [HR] = 0.73, *p* = 0.001) with an almost 50% reduction in intrathoracic recurrences. The randomized phase II RTOG-0937 trial was designed to evaluate PCI ± consolidative RT to intrathoracic disease and limited extracranial metastases in ED-SCLC patients. Results of RTOG-0937 showed that consolidative RT prolonged progression free survival (PFS), but did not improve 1-year overall survival (OS) [3]. Since both studies provide interesting signals for a potential benefit of local thoracic consolidation, but failed to reach statistical significance within their trial designs, a controversial discussion about who might profit from thoracic radiotherapy is ongoing. Based on German guidelines (Onkopedia and consultation version of new S3-guideline), thoracic radiation can be offered to patients with residual disease following systemic treatment on an individual basis. This is in line with the ESMO guidelines, which mention consolidation radiotherapy to the residual tumor and lymph nodes as a treatment option (grade C, level II recommendation) for patients with a performance score of 0-2 who achieve a response after chemotherapy, while the ASTRO guidelines strongly recommend thoracic radiotherapy for patients with a response to chemotherapy alone but residual tumor in the thorax. At the same time, all guidelines stress that there is a lack of data considering the implementation of consolidation thoracic radiotherapy to immunochemotherapy in ED-SCLC. The advent of immunotherapies has revolutionized the management of several tumor entities, including advanced non-small cell lung cancer (NSCLC). Here, upfront mono- or combination therapies with immune checkpoint inhibitors (ICI) are now standard of care in the majority of patients. Considering their high mutational burden, SCLC tumors were also expected to respond well to this type of treatment. Indeed, results from several clinical trials suggest that SCLC patients may benefit from such therapies [4, 5]. In particular, the addition of a programmed death-ligand 1 (PD-L1) checkpoint inhibitor to chemotherapy in order to enhance T cell-mediated immunity appears to be very promising, as was demonstrated by the results of the IMpower133 trial [6]. Here, adding the PD-L1 antibody atezolizumab to carboplatin/etoposide induction therapy followed by an atezolizumab maintenance therapy significantly prolonged OS and PFS compared to the placebo arm. Results of the CASPIAN phase 3 study, where combination of platinum-etoposide with durvalumab in first-line treatment for patients with ED-SCLC resulted in stable and persistent clinical benefit across OS, PFS, and objective response [7], align with Impower133 trial findings. Addition of pembrolizumab (anti-PD-1) to etoposide and platinum treatment, as part of the KEYNOTE 604 study, significantly prolonged PFS in comparison with placebo plus etoposide and platinum as first-line therapy for patients with ED-SCLC [8]. Despite these encouraging data on outcome, the question remains how the response can be further increased.

Along this line, the combination of photon radiotherapy with immunotherapeutic approaches has recently caught attention as an attractive approach for treatment of lung cancer. The rationale behind this lies in the capability of radiotherapy itself to promote immune-mediated anti-tumor responses through a variety of processes, such as inducing the immunogenic death of tumor cells resulting in antigen release and broadening of the immune repertoire of T cells, the enhancement of chemokine-mediated T cell recruitment towards the irradiated tumor, or the upregulation of major histocompatibility complex I (MHC I) and tumor-associated antigens that increase tumor cell vulnerability [9]. The radiation-induced effects on the microenvironment and the activation of immune cells can result in tumor regression even distant from the irradiated field, a phenomenon that has been first observed in the 1950s and is referred to as the “abscopal effect” [10]. Several clinical trials started to explore the combination of ICI and radiotherapy. In unresectable NSCLC stage III, the PACIFIC trial has proven an immense clinical impact of treatment with durvalumab after chemoradiotherapy with notably low toxicities resulting in the approval of this regimen [11, 12]. In the phase II DETERRED trial, concurrent atezolizumab administration with chemoradiation therapy (CRT) followed by consolidation and maintenance atezolizumab did not show increased toxicities compared to CRT alone followed by consolidation and maintenance atezolizumab [13]. Furthermore, recent analyses have also suggested a good tolerability of the combination of immunotherapeutic drugs and radiotherapy in patients with different solid tumors [14–16].

The TREASURE trial presented here combines the IMpower 133 regimen with thoracic radiotherapy and will explore efficacy and feasibility of this treatment. The objectives of this trial are to: i.) increase the efficacy of chemotherapy combined with atezolizumab by adding radiotherapy, ii.) assess the safety and tolerability of the combination of chemotherapeutic, immunological and radiological treatment in the first-line setting of advanced SCLC, and iii.) collect tumor tissue, blood and stool samples for translational research.

## Methods/design

### Study design, setting, objectives, and characteristics of participants

The TREASURE trial is an open-label, randomized, multicenter phase II clinical trial to examine the feasibility and treatment efficacy of TRT with the IMpower133 regimen in first-line treatment of patients with advanced SCLC. The main objective is the increase of efficacy of atezolizumab maintenance after induction with chemo-immunotherapy by adding TRT. Secondary objectives include the determination of safety and tolerability of radiological and immunological treatment in the first-line setting of ED SCLC and the prospective biomaterial collection for an accompanying translational research program. This study will be performed in compliance with the Declaration of Helsinki principles, and the protocol was accepted by the responsible institutional review boards.

In total, one hundred four patients are planned to be included in twenty sites across Germany and Austria within 24 months. Clinicaltrials.gov (NCT04462276) provides access to a complete list of sites. Recruitment began in September 2020 (First Patient In) and will be finalized in July 2024.

Upon arrival at the clinic, patients who may be eligible for study inclusion will be approached and invited to participate. At time of inclusion into the study, all patients must have been diagnosed with ED SCLC and responded to four cycles of induction therapy with carboplatin/ etoposide and atezolizumab, which they have received independently of the study as part of standard of care therapy (Fig. 1). Before study enrolment, all documents and their imaging files will be reviewed by a board-certified radiation oncologist, as to whether or not the thoracic tumor formation can safely be treated by thoracic radiotherapy – based upon the expected target coverage and sparing of critical organs, such as the lungs. The main eligibility criteria are specified in Table 1.

**Fig. 1 Fig1:**
[figure not shown]
TREASURE study design. ED SCLC patients with any response (defined as CR/PR or thoracic SD with CR/PR of extrathoracic lesions) after four cycles of standard chemo-immunotherapy consisting of carboplatin/etoposide and atezolizumab will be randomized to either receive thoracic radiotherapy or not. All patients will receive maintenance atezolizumab therapy until disease progression or occurrence of intolerable toxicities

**Table 1 Tab1:** Key inclusion and exclusion criteria of the TREASURE trial

Inclusion criteria	Exclusion criteria
• Fully-informed written consent • Confirmed ED SCLC • ECOG performance status score ≤ 1 • Any response after four cycles of induction chemo-immunotherapy defined as CR/PR or thoracic SD with CR/PR of extrathoracic lesions • Thoracic treatment volume considered treatable using acceptable radiation fields as judged by a radiation oncologist • 28 ± 7 days between last administration of chemo-immunotherapy and randomization. • Patients with a history of treated CNS metastases are eligible, if there is no ongoing requirement for corticosteroids as therapy for CNS disease. Patients with asymptomatic brain metastases that do not require local therapy with irradiation (whole brain irradiation) can be included. • No previous radiotherapy to lung and mediastinal lymph nodes within the past 5 years • Availability of pre-treatment tumor tissue specimen • FEV1 ≥ 40% • Adequate bone marrow, renal function, and hepatic functions	• Prior treatment with immunotherapeutic drugs (with the exception of induction chemo-immunotherapy as defined in inclusion criteria) • Prior therapy for limited-stage SCLC with curative intent • History or current radiology suggestive of interstitial lung disease (ILD) (including but not limited to idiopathic pulmonary fibrosis (IPF), formerly described as usual interstitial pneumonia (UIP), and cryptogenic fibrosing alveolitis (CFA)), non-infectious pneumonitis, drug-induced pneumonitis, idiopathic pneumonitis. • Any concurrent cancer treatment or major surgery (as defined by the Investigator) • Active or prior documented autoimmune or inflammatory disorders or history of active primary immunodeficiency • Current use of immunosuppressive medication • Positive testing for hepatitis B virus surface antigen (HBV sAg), hepatitis C virus ribonucleic acid (HCV RNA), or human immunodeficiency virus (HIV) • History of another primary malignancy except for malignancies treated with curative intent and no known active disease ≥3 years before first dose of study medication • Any co-existing medical condition that in the investigator’s judgement will substantially increase the risk associated with the patient’s participation in the study.

### Study procedures

Before a patient’s involvement in the clinical study, the investigator is under obligation to obtain written informed consent. The randomization will be done by a validated program using variance minimization method [17]. All randomization design aspects and patient allocation statuses underly strict access control. The allocation of the patient numbers and treatment groups will be coordinated by an Interactive Web Response System (IWRS) system integrated in the eCRF. After 1:1 randomization, eligible patients will receive either atezolizumab (1200 mg fixed dose, every 3 weeks [Q3W]) and TRT (30 Gy in 10 fractions) in arm A or atezolizumab only (1200 mg fixed dose, Q3W) in arm B. Patients will be stratified during randomization according to presence of brain metastases (yes vs no), thoracic response after induction therapy (complete/partial response [CR/ PR] vs stable disease [SD]), and prophylactic cranial irradiation PCI (yes vs no). Treatment will be discontinued in case of progressive disease, unacceptable toxicity, on patients’ request, or at the end of study.

In order to ensure patient safety with regard to a potential increase in risk of treatment-related pneumonitis when combining TRT with immune checkpoint inhibition, a safety interim analysis will be performed in arm A after *n =* 23 patients have been followed for 3 months after the end of TRT. If in this cohort the number of patients with a grade ≥ 3 pneumonitis is 2 or more, recruitment to the trial will be stopped. All evaluations will be performed by the medically responsible experts of this trial, i.e. the Coordinating Investigator, the Deputy Coordinating Investigator and the Mentoring Coordinating Investigator– under support of the study statistician as far as applicable. They will provide their opinion to the Sponsor or its delegate who will be responsible for the formal decision on termination / continuation. The Safety Monitoring Committee (SMC) will additionally review all evaluations / decisions and provide its opinion to the Sponsor.

During treatment, tumor response will be assessed according to Response Evaluation Criteria in Solid Tumors (RECIST), version 1.1 by radiological imaging by computed tomography (CT) and/or magnetic resonance imaging (MRI) of the chest and upper abdomen at baseline, then every 6 weeks for the first 36 weeks, and every 9 weeks thereafter until occurrence of disease progression, according to the standard of care. After treatment discontinuation for reasons other than progressive disease, imaging will be performed accordingly to the above-mentioned schedule until progression, death, initiation of another anti-cancer therapy according to the standard of care or end of study. After the end of study, subjects will be proactively followed up regarding treatment-related adverse events until resolved, returned to baseline or deemed irreversible, until lost to follow-up, or withdrawal of study consent. All patients will be followed for survival. Follow-up by phone every 3 months (every 12 weeks [Q12W] ± 14 days) will be offered to patients who decline to return to the site for evaluations. The investigators of the study are responsible for the further treatment of the patient after the end of the study treatment for disease progression and shall support and advice the patients.

Safety assessment during this trial will include physical examinations, Eastern Cooperative Oncology Group (ECOG) performance status, clinical laboratory profile and continuous assessments of adverse events. The brief summary of all study procedures is presented in Table 2. An electronic case report form (eCRF) will be filled by the principal investigator or authorized study stuff person for each participant for data collection throughout the entire trial. The investigator must obtain written informed consent before patient participates in the clinical study. In addition, an adjudication committee has been established to exclude interstitial lung disease (ILD) in all pre-screened patients prior to study inclusion. All observed toxicities and side effects will be recorded in the eCRF and graded according to National Cancer Institute Common Terminology Criteria for Adverse Events (NCI-CTCAE) v5.0 for all patients and their relationship to all study treatment/ procedures assessed and summarized.

**Table 2 Tab2:** Schedule of assessments

Procedure/ Point in Time	Screening	Treatment				Post- Treatment		
	Inclusion	C1D1	Each cycle (q2w ± 3 days)	Every second cycle (q4w ± 3 days)	EOT	Safety FU-1*	Safety FU-2**	FU (q12w ± 14 days)
Central review – ILD exclusion^#^	(x)							
Informed consent, eligibility criteria, demographics, medical and disease history	x							
Prior and Concomitant Medication Review	x	x	x		x			
Allocation/Randomization	x							
Vital Signs, O_2_ Saturation, and Weight	x	x	x		x	x	x	
ECOG Performance Status	x	x	x		x			
Pregnancy Test, CBC with Differential, Serum Chemistry Panel, Thyroid function test	x	x	x		x			
Urinalysis	x	Whenever clinically indicated						
12-lead ECG	x	Whenever clinically indicated						
Pulmonary function tests	x	x^a^		together with staging	x	x	x	
AEs	x	x	x		x	x	x	x
Full Physical Examination	x							
Directed Physical Examination		x	x		x	x	x	
FACT-L questionnaire	x	x		x	x	x	x	(x)
Tumor Imaging	x	(x^b^)		(x^c^)	(x^d^)			(x^d^)
Tissue	x	Optional: Re-Biopsy at time of progression						
Blood and stool	x	(x^e^)	x	x	x			
Atezolizumab administration		x	x					
Radiotherapy (Arm A^f^)		x						

^#^: A sponsor-independent adjudication committee was established to exclude interstitial lung disease (ILD) [Excl. criterion 5] in all pre-screened patients prior to study inclusion. All study sites are encouraged to provide tumor imaging in pseudonymize form during the (pre-)screening phase for the central review process

*: The regular 30-day full safety follow-up period (FU-1) begins on the day after the EOT visit and lasts approximately 30 days. The FU-1 visit occurs at or near the end of the 30-day safety follow-up period (±7 days)

**: The regular 90-day full safety follow-up period (FU-2) begins on the day after the EOT visit and lasts approximately 90 days. The FU-2 visit occurs at or near the end of the 90-day safety follow-up period (±7 days)

^a^: To be performed on C1D1 if in accordance with local standard

^b^: Chest X-ray to be performed on cycle 1 if in accordance with local standard

^c^: First on-study imaging to be performed 6 weeks (± 7 days) after baseline imaging. Further on-study imaging to be performed Q6W (42 days ±7 days) for the first 36 weeks, and every 9 weeks (±7 days) thereafter until occurrence of disease progression, according to the standard of care

^d^: Only applicable if EOT not according to already detected disease progression

^e^: Biomarker sample to be taken prior to first study drug medication or before first administration of thoracic radiotherapy for arm A, either during screening or C1D1 visit

^f^: Patients in arm A receive thoracic radiotherapy with a dose fractionation of 10 × 3 Gy (30 Gy) within 2 weeks (+ 7 days) in combination with atezolizumab treatment. Thoracic radiotherapy to be started within 7 weeks after C4D1 of induction therapy

The Institute for Clinical Cancer Research (IKF) at Northwest hospital in Frankfurt (Germany) will be responsible for data management and data quality assurance following current Standard Operational Procedures (SOPs) of the IKF.

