### Study endpoints

The primary endpoint of the TREASURE trial is OS defined as time from randomization to death due to any cause. Secondary efficacy endpoints include 1- and 2-year OS rates, PFS, response rate, and the intrathoracic tumor control defined as rate of intrathoracic progression and time to intrathoracic progression. Moreover, safety will be assessed by evaluating the incidence, nature, causal relationship and severity of adverse events according to CTCAE v5.0 (with special focus on pulmonary events including pneumonitis; hepatic, gastrointestinal, endocrine, ocular, dermatologic, renal and pancreatic events including pancreatitis; immune-mediated myocarditis and myositis as well as infusion-related reactions and cytokine-release syndrome) and the frequency of abnormal laboratory parameters, and feasibility will be addressed in terms of frequency of treatment withdrawal, i.e. due to adverse events or other reasons, and completion of radiotherapy. Furthermore, cancer-related quality of life will be measured using the Functional Assessment of Cancer Therapy – Lung (FACT-L) questionnaire. The planned biomarker analysis of biomaterials that will be collected during the clinical trial is an exploratory endpoint of the TREASURE study.

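### Scheduled imaging ends at the first progression at any site, so the crude intrathoracic progression rate mixes thoracic control with extrathoracic relapse and death

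*Protocol article*

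**What the plan says.** All references are to the protocol article.

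- **Endpoint (Study endpoints).** One secondary efficacy endpoint is "the intrathoracic tumor control defined as rate of intrathoracic progression and time to intrathoracic progression". Nothing limits it to the first site of failure.
- **Imaging on treatment (Study procedures; repeated in Table 2, footnote c).** After the baseline scan, imaging is repeated "every 6 weeks for the first 36 weeks, and every 9 weeks thereafter until occurrence of disease progression, according to the standard of care". Each scan takes in both the thorax and the upper part of the abdomen.
- **Imaging after stopping treatment for a reason other than progression (Study procedures).** It follows the same "schedule until progression, death, initiation of another anti-cancer therapy according to the standard of care or end of study".
- **End-of-treatment and follow-up imaging (Table 2, footnote d).** "Only applicable if EOT not according to already detected disease progression".
- **Treatment and later follow-up (Study procedures).** "Treatment will be discontinued in case of progressive disease", again without naming a site. After that, "All patients will be followed for survival".
- **Analysis (Methods of statistical analysis).** Secondary endpoints are analysed descriptively. Chi-squared tests are named for group comparisons of ordinal or dichotomous variables.
- **Rationale (Background).** Radiation effects "can result in tumor regression even distant from the irradiated field" are described as a possibility.

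**The concern.** TRT treats the chest, so intrathoracic control is the secondary endpoint closest to its local action. As worded, the endpoint covers every intrathoracic progression. As scheduled, the imaging observes the chest only until something progresses anywhere. A patient whose first relapse is outside the chest leaves scheduled thoracic observation at that point, whatever the chest does later.

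The proportion with observed intrathoracic progression therefore depends on how long patients stay free of extrathoracic relapse and death, as well as on how well the chest is controlled. If TRT also altered extrathoracic relapse, the arms would be under thoracic observation for different lengths of time, and a comparison of crude proportions would carry that difference. An analysis plan can choose a suitable estimator for what is observed. It cannot recover scans that were never scheduled.

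**Working it through.** **1. Endpoint against schedule.** The endpoint is unrestricted intrathoracic progression. All three imaging rules (on treatment, off treatment, and end of treatment or follow-up) stop at progression at any site. The off-treatment rule also stops at new anti-cancer therapy. The article schedules no chest imaging after an extrathoracic-only progression. What the schedule observes is intrathoracic progression at or before first progression.

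**2. Inputs for the size.** The article gives no intrathoracic progression rate, so there is no stated figure to reproduce. All hazards below are assumptions: constant monthly hazards in arm B of t = 0.10 (intrathoracic), e = 0.08 (extrathoracic) and d = 0.01 (death), over 24 months.

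**3. Formula.** With s = t + e + d, the crude rate is (t/s) × (1 − exp(−24s)).

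Arm B: s = 0.19 and 1 − exp(−4.56) = 0.9895. The crude rate is 0.10/0.19 × 0.9895 = 52.1%. The share leaving thoracic observation through extrathoracic relapse is 0.08/0.19 × 0.9895 = 41.7%.

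**4. Arm A under different effects.**

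| Intrathoracic HR | Extrathoracic HR | t, e, d | Crude rate, arm A | Ratio to 52.1% |
|---|---|---|---|---|
| 0.50 | 1.0 | 0.05, 0.08, 0.01 | 34.5% | 0.66 |
| 0.50 | 0.80 | 0.05, 0.064, 0.01 | 38.3% | 0.73 |
| 0.50 | 0.50 | 0.05, 0.04, 0.01 | 45.5% | 0.87 |
| 0.70 | 0.60 | 0.07, 0.048, 0.01 | 52.2% | 1.00 |
| 1.0 | 0.60 | 0.10, 0.048, 0.01 | 61.9% | 1.19 |

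A ratio of risks need not equal a hazard ratio in any case. The evidence is in the first three rows: the thoracic effect is identical, yet the crude ratio moves from 0.66 to 0.87 because of the extrathoracic hazard alone.

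**5. The time-to-event half.** In the same model, take the row with HRs 0.70 and 0.60. Expected person-months up to first event are (1 − exp(−24s))/s: 0.9895/0.19 = 5.21 in arm B and 0.9537/0.128 = 7.45 in arm A. The intrathoracic event rates are 0.521/5.21 = 0.100 and 0.522/7.45 = 0.070, so the cause-specific hazard ratio is 0.70. The true thoracic effect is recovered although the crude rates are equal.

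**6. What falls outside scheduled imaging.** A simulation of 400,000 patients per arm kept t = 0.10 and d = 0.01 in the control arm. It assumed an extrathoracic hazard of 0.04 to 0.12, death at 0.09 per month after progression, and an intrathoracic hazard after extrathoracic relapse of one or two times the earlier one.

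- Stopping at first progression missed about 16% to 45% of control-arm intrathoracic progressions.
- If TRT halved only the intrathoracic hazard, the first-event rate ratio was 0.63 to 0.70, against 0.70 to 0.77 had imaging continued. Truncation then makes TRT look better.
- If TRT left the intrathoracic hazard unchanged and halved the extrathoracic hazard (0.08 to 0.04, multiplier one), the first-event ratio was about 1.24 (52% to 65%), against about 1.06 (73% to 78%) with imaging continued. Truncation then makes TRT look worse.

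The direction of the distortion is therefore not fixed.

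**The case against.** **The strongest case against** is that the schedule already supports a valid measure of local control. The scan covers chest and upper abdomen together, so thoracic failure before a first progression, or on the same scan, is captured. Time to intrathoracic progression, censored at extrathoracic relapse, recovers the thoracic hazard ratio in step 5. Competing-risk handling and censoring rules commonly sit in the full protocol or the analysis plan. The list of secondary tests is evidently condensed, since it names no time-to-event method even for progression-free survival. Stopping at progression is also defensible: study treatment ends then, and later thoracic status would reflect non-randomised therapy.

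Most of this stands. A reader might infer that later intrathoracic progression is never seen, or that local control cannot be measured. The article supports neither. It ends scheduled imaging but does not bar standard-of-care scans afterwards, although these would be unscheduled and possibly unequal between arms. Control up to first progression is measurable.

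**The scenarios** can also be challenged. Those in which a local benefit vanishes or reverses need an extrathoracic hazard ratio of about 0.60. The Background describes distant regression only as something that can occur, and no stated objective claims distant benefit. For the phase III trial whose radiotherapy is followed here, the Background reports a progression hazard ratio of 0.73 with intrathoracic recurrences nearly halved. With the assumed arm B hazards, intrathoracic HR 0.50 and extrathoracic HR 1.0 give an any-progression HR of (0.05 + 0.08)/0.18 = 0.72. That is close to the reported figure, and in that case the crude ratio is 0.66 and the benefit is visible. Those data come from chemotherapy without immunotherapy, so they do not settle the matter for this trial.

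**What remains** is a mismatch between two items that the article does state: an endpoint covering all intrathoracic progression, and a schedule that stops at any progression. It does not depend on censoring details the article leaves out.

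**Conclusion.** The point holds as a mismatch between endpoint and observation. The overall rate of intrathoracic progression, as defined, is not systematically observable, and the crude observed rate is not a clean measure of thoracic control. With the thoracic effect fixed at HR 0.50, the crude ratio runs from 0.66 to 0.87 as the extrathoracic HR goes from 1.0 to 0.50. With no thoracic effect and extrathoracic HR 0.60 it is 1.19. These figures rest on assumed constant hazards; the article quantifies neither the hazards nor any extrathoracic effect of TRT.

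A reader might go further and conclude that the trial is set to hide a local benefit or show local harm. The article does not support that: it would require a substantial extrathoracic effect, and without one the distortion can run the other way. The time-to-event component remains interpretable as a cause-specific hazard up to first progression.

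This is a minor-to-moderate correction to one secondary, descriptively analysed endpoint. Overall survival and the pneumonitis stopping rule are unaffected.

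**What to change.** 1. In Study endpoints, define intrathoracic control as intrathoracic progression at or before first RECIST progression.
2. Report its cumulative incidence by arm, with extrathoracic-only progression and death as competing events, and show the extrathoracic cumulative incidence beside it.
3. Compare the arms by the cause-specific hazard ratio, adjusted for the stratification factors (brain metastases, thoracic response after induction, PCI).
4. Do not use the crude rate, or a chi-squared test of it, as the measure of local control.
5. Where standard-of-care chest scans exist after extrathoracic progression, thoracic status may be recorded in the eCRF as supportive data only, because such scans are unscheduled and follow non-randomised therapy.

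**Cost.** A change to the endpoint wording, one competing-risk analysis and, if item 5 is adopted, one eCRF item. No scan is added and treatment is unchanged. The downside is that the claim narrows to thoracic control up to first progression, which is all that the schedule can support.
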